### **Suspected Unexpected Serious Adverse Reaction (SUSAR)**

All adverse events, considered as related to the study drug(s) (study drug (glenzocimab or placebo) and which are unexpected and serious (SUSARs) are subject to expedited reporting to the Competent Authorities (CAs) and to the Ethics Committees (EC), in compliance with the local regulatory requirements.

The sponsor or designate will be responsible for reporting the SUSARs, on the basis of the information provided by the investigator.

#### **9.7.2 Reporting**

##### **Reporting of SAEs, SUSARs or Serious Safety-related Protocol Deviations and Measures for Prompt Communication**

The investigator informs the sponsor of all SAEs (expected and unexpected) whether or not considered as related to the study drug(s) (glenzocimab or placebo) which occur during the study from the signature of the study informed consent and until 30 days after the last dose of the IMP.

The SAE must be reported by the investigator **immediately, or within no more than 24 hrs from the date of the first awareness to the PV department of AIXIAL** (*see Appendix 5*).

The SAE report form must be signed and dated by the principal investigator or by any other investigator designated by the principal investigator as authorized to notify safety issues.

All available information concerning the SAE (anonymous copies of laboratory results, other examinations, hospitalization reports, autopsy report and all other relevant documents) will be transmitted anonymously with the SAE report form.

Further to the notification of a SAE, additional information relative to the SAE may be requested by the sponsor or its representative (by fax, telephone, mail or visit). The investigator must respond to these requests for additional information.

All SAEs must be documented in the patient's medical file, and the SAE report forms (initial report and follow-up reports) must be kept in the investigator's file.

The full requirements of the "ICH Guideline for Clinical Safety Data Management, Definitions and Standards for Expedited Reporting, Topic E2" will be adhered to. The study will be conducted in compliance with all local regulatory requirements.

In compliance with the provisions set forth in the EU guideline issued in July 2017 (EMA/CHMP/SWP/28367/07 Rev. 1) related to early clinical trials, particular care should be paid to the following:

- All study staff (investigator's, sponsor's, sponsor's representatives and vendors involved in the conduct, monitoring, follow-up or reporting of the present trial should be appropriately trained to the detection, handling, and reporting of the SUSARs, SAEs, and important medical events, with a particular emphasis on those possibly related to a SICH.
- A 24/7 responsible point of contact will have to be in place (with available telephone number) both at sponsor's representative CRO, and at the pharmacovigilance hub (AIXIAL), with for this latter, a direct access to the randomization code, in case of an emergency unblinding (see [Section 6.3.3](#)).

- In case a particular related SAEs or the number of defined for triggering an immediate decision on trial continuation need that the inclusions of new patients in the study are immediately suspended, this information should be immediately communicated to the central randomization unit, and to all investigators, participants involved at any site, at least prior to the next dosing. This information should also contain the implementation of corrective or preventative measures to the extent necessary.

The detailed flowchart for processing such information is included in Follow-up of Serious Adverse Events

For any new information concerning an SAE that has already been notified, the investigator must complete a new SAE report form (follow-up report) which will be sent by email **immediately, or within no more than 24 hrs** to the **PV Department of AIXIAL**, accompanied by anonymized copies of the corresponding laboratory results, other examinations and/or hospitalization reports.

The reporting of the SAE follow-up information will be done in the same manner as the initial SAE reports.

Any SAE regardless of relationship to the IMP must be followed until its resolution or stabilization (in case of sequelae). This may lead to the follow-up of the patient beyond the study period.

### **Serious Adverse Events occurred after the study**

No active screening of potential Serious Adverse Events occurring after study discharge (40 days post treatment administration) is expected. However, in case an SAE considered as reasonably related to the study drug(s) (*glenzocimab or placebo*) or to a study procedure would occur after study end, this SAE must be reported to the sponsor or its representative(s) according to the same reporting procedure. It would be forwarded to the competent authorities as for routine pharmacovigilance, analysed and maintained in the product safety database.

### **Pregnancy**

Pregnancy is an exclusion criterion of study but if a patient becomes pregnant within 4 months after the study drug injection, the pregnancy must be reported;

Pregnancies must be reported by the investigator, like SAEs, within 24 hrs of awareness.

The reporting of pregnancy will be done according to the procedure used for the SAEs reporting.

The sponsor or its representative must follow each pregnancy to term.

The pregnancy outcome must be reported by the investigator, to the sponsor or its representative.

## **10. DATA HANDLING**

### **10.1 CASE REPORT FORM (CRF)**

An electronic data capture system will be used for this study. An electronic CRF (eCRF) is designed to record all the data required by the protocol and collected by the Investigator in compliance with Sponsor specifications and requirements regulatory.

Data entry at the investigator's site will be performed by the Investigator or by the designed person from his/her team using the eCRF screens designed with web technologies.

Data entered via the Internet will be directly recorded in the study database.

The Investigator or the designated person from his/her team agrees to complete the eCRF, at each patient visit, and all other documents provided by the Sponsor.

All corrections of data on the eCRF must be made by the Investigator or the designated person from his/her team using electronic data clarifications according to the provided instructions. Any data modification will be recorded in chronological order using the audit trail feature of Oracle inForm database, including date and reason for modification.

In order to ensure confidentiality and security of the data, usernames and passwords will be used to restrict system access to authorized personnel only, whether resident within the investigator's sites, Sponsor or third parties.

The monitor must make certain that all data are completed on the eCRF.

After the last visit of the participant and the lock of the eCRF by the Data Management Department, the Investigator must attest by entering his/her user name and password:

- the authenticity of the data collected in the eCRF;
- the coherence between the data in the eCRF and those in the source documents, with the exception of those data recorded directly in the eCRF and considered as source data.

After comparing the data to the source documents, the monitor will request corrections/clarification from the Investigator using electronic data clarifications using functionalities on line of Source Data Verification.

## 10.2 DATA MANAGEMENT

SAS® software version 9.3 or later is used for data management process and data are stored in the clinical database stored in a secure folder.

The Data Management Department of the CRO is responsible for data processing including drafting of Data Management Plan, development of Data base structure, drafting the Data Validation Plan (list of edit checks, and SAS Listings), data transfer, SAE reconciliation and data coding: medical history, adverse events and signs and symptoms are coded using the current version of the MedDRA. Prior and concomitant medications are coded using World Health Organization (WHO) drug dictionary (last version available).

When data validation is completed, a review of the data is performed according to the CRO standard operating procedure.

A final database will be declared when all data has been entered, the data validated and the database defined as clean by the Data Manager. After declaration of a final database, the data will be exported from the database to SAS datasets and both the database and the SAS datasets will be frozen and protected from changes. All statistical analyses for the final analysis will be performed on the frozen SAS datasets

## 11. STATISTICAL METHODS

Complete details of the statistical analyses will be provided in the Statistical Analysis Plan (SAP) which will be finalized prior to the locking and unblinding of the database.

Any modification of the initial statistical method and the reason why they were performed will be described in a specific section of the study statistical analyses plan (SAP) as well as in the clinical study report.

### 11.1 General considerations

In general, summary tabulations will be presented by treatment arm and will display the number of observations, mean, standard deviation, median, minimum, and maximum for continuous variables, and the number and percent per category for categorical data. The Kaplan-Meier survival curves and 25th, 50th (median), and 75th percentiles will be provided along with their 2-sided 95% confidence intervals (CIs) for time-to-event data.

The nominal one-sided alpha level of significance considered for statistical tests will be 0.025.

As this is essentially an estimation study, no adjustment for multiplicity will be proposed.

Methods for handling missing data will be further detailed in the SAP.

### 11.2 Randomization and Stratification

Eligible patients will be randomized in a 1:1 allocation ratio either to ACT017 or placebo. Details on the randomization process will be described separately.

### 11.3 Analysis Sets

- **Safety set:** All enrolled patients having received at least one dose of the prescription of study medication (either ACT017 or placebo). The Safety set will be the basis for safety analyses. Patients will be assigned to the treatment group as treated for the Safety set.
- **Randomized Set (ITT set):** All patients who are randomized into the study and considered as randomized, i.e. with study drug assignments designated according to initial randomization, regardless of whether subjects received what was assigned. Sensitivity efficacy analyses conducted on ITT set could be considered.
- **Full Analysis Set (FAS):** All randomized patients having received at least one dose of the prescription of study drug (either ACT017 or placebo). Patients will be assigned to the treatment group as randomized (i.e. with study drug assignments designated according to initial randomization, regardless of whether subjects received what was assigned). The FAS will be considered as the primary set for efficacy analyses.
- **Per protocol (PP) set:** All FAS patients without any major protocol deviation. Major protocol deviations will be identified during data review meetings that will be held before unblinding and database lock.

### 11.4 Sample Size Determination

As this is essentially an exploratory study which aim is to estimate the treatment difference in order to better design the future trials, the sample size cannot be justified on a formal power calculation based on a reasonable expected difference.

60 (sixty) patients are considered sufficient to estimate the treatment effect on the efficacy parameters.

As a rough order of magnitude, if the true death rate is assumed to be 0.4 in the placebo group, then a true death rate of 0.10 should be assumed to achieve at least a 80% power to detect this difference in rates at the 1-sided alpha level of 0.025, using an unpooled variance Z test. If the true death rate is assumed to be lower, such as 0.3 in the placebo group, then a true death rate of 0.04 should be assumed to achieve at least a 80% power to detect this difference in rates at the 1-sided alpha level of 0.025, using an unpooled variance Z test.

Assuming a dropout rate of 12%, 68 patients will be enrolled in this study.

With regard to the primary safety endpoint, 60 (2X30) patients randomized will be sufficient to observe in the ACT017 arm at least one serious adverse event which incidence is greater than or equal to 5% with a probability of at least 79%.

## 11.5 Analyses

### 11.5.1 Efficacy Analyses

Full details of the analysis of efficacy endpoints will be provided in the SAP.

#### **Primary efficacy endpoint: Progression from moderate to severe respiratory distress assessed at Day 4**

Progression from moderate to severe respiratory distress assessed at Day 4 is a composite failure endpoint defined as the occurrence of at least one of the following failure events at Day 4 :

- $RR \geq 30/\text{min}$ , or
- $SpO_2$  decrease  $> 5\%$  in ambient air. In case where oxygenotherapy cannot be discontinued, please refer to NEWS 2 Scale (item  $SpO_2$ , scale 2) for adequate conversion (e.g. 93-94 on  $O_2$  corresponding to 86-87 in ambient air),
- $PaO_2/FiO_2 \leq 100\text{mmHg}$
- Death occurring prior to or on Day 4

The composite event rate will be estimated within each group. The difference in composite event rates and the odds ratio will be estimated along with their asymptotic and exact 95% confidence intervals. p-values from the chi-square and exact Fisher test will also be provided.

#### **Handling missing data:**

When the composite endpoint contains missing components, the composite endpoint is a failure if at least one non missing component is a failure. If all non missing components are successes, the composite endpoint is not computable and missing components should be imputed. In that latter case, a procedure for imputing missing components depending on the status of the last available component value (failure or success) will be proposed and detailed in the SAP.

**Component-wise secondary analysis:** an analysis of each individual binary component will be performed as an aid to the interpretation of the overall result of the composite. The difference in component event rates and the odds ratio will be estimated along with their asymptotic and exact 95% confidence intervals. p-values from the chi-square and exact Fisher test will also be provided. No adjustment for multiplicity will be used.

Multi-component analysis: an additional secondary analysis will be performed to assess the proportion of patients with one failure only, 2 failures and 3 failures among the 3 components (except death).

Sensitivity analyses will be proposed and detailed in the SAP.

Additional analyses of the primary endpoint: the primary composite endpoint will be analyzed in a logistic regression model including treatment effect and relevant covariates ( e.g. baseline WHO-Covid-19 scale) that will be specified in the SAP.

Subgroup analyses:

If feasible (i.e. when subgroup sizes are sufficient), subgroup analyses of the primary endpoint will be performed by BMI ( <30 vs >=30 ), Age (< 60 vs >=60) , by baseline WHO-Covid-19 scale , comorbidity, concomitant medications will be provided and further detailed in the SAP.

The same analysis proposed for the primary efficacy endpoint assessed at day 4 will be provided at other time points (Days 1, 2, 3, 7, 14, 20 and 40). The primary endpoint and its components will also be described via plots (e.g., stacked bar plots representing the proportion of subjects in each category (failure or not) , by treatment arm, over time).

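### The primary Day 4 estimate is fixed as a crude risk difference although baseline respiratory rate and PaO2/FiO2 are in hand; adjusting for them would be a cheap gain in precision if they are prognostic

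*Protocol*

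**What the plan says.** The primary endpoint is failure at Day 4: RR of 30/min or more, an SpO2 fall of more than 5%, PaO2/FiO2 of 100 mmHg or less, or death. Section 11.5.1 fixes its analysis: "The difference in composite event rates and the odds ratio will be estimated along with their asymptotic and exact 95% confidence intervals", with chi-square and Fisher p-values. All of this is unadjusted.

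Adjustment comes later in the same section, as an additional analysis: "the primary composite endpoint will be analyzed in a logistic regression model including treatment effect and relevant covariates ( e.g. baseline WHO-Covid-19 scale". The sentence ends by leaving the covariates to the SAP.

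Other parts of the protocol bear on this:

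- Section 7.3 lists RR, SpO2 and PaO2/FiO2 among the examinations done before randomisation.
- Section 5.1.1, criterion 5, admits patients with any one of RR of at least 24, SpO2 of 93% or less, or PaO2/FiO2 of 200 or less, provided that RR is below 30 and PaO2/FiO2 is above 100.
- The Day 40 mortality model in section 11.5.1 includes baseline respiratory status on each primary component, coded as moderate or not. The WHO and NEWS-2 comparisons are stratified by their own baselines.
- Section 11.1: "As this is essentially an estimation study, no adjustment for multiplicity will be proposed". Section 11.4: "60 (sixty) patients are considered sufficient to estimate the treatment effect on the efficacy parameters".

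**The concern.** Two of the failure criteria are fixed thresholds on RR and PaO2/FiO2, and both were measured about four days earlier. Someone entering at RR 29 or a ratio of 105 starts close to failing; someone entering at RR 24 or a ratio of 195 does not. Because one sign suffices for entry, the baseline spread can be wide. The crude difference uses none of this information.

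The protocol is also uneven. It names baseline respiratory status for a mortality endpoint 36 days later, but commits to no such covariate for the endpoint built from those measures.

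The trial exists to estimate a treatment difference for planning later studies. What is at stake is the width of that interval, and how far chance imbalance in baseline severity moves the estimate.

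**Working it through.** **The protocol's own figures.** Section 11.4 claims at least 80% power with an unpooled Z test at one-sided 0.025 and 30 per arm: "if the true death rate is assumed to be 0.4 in the placebo group, then a true death rate of 0.10 should be assumed" and, in the second scenario, "such as 0.3 in the placebo group, then a true death rate of 0.04 should be assumed". Power = Φ(|p1−p2| / √(p1q1/30 + p2q2/30) − 1.96).

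- 0.40 v 0.10: 0.30/√((0.24+0.09)/30) = 2.860; Φ(0.900) = 81.6%.
- 0.30 v 0.04: 0.26/√((0.21+0.0384)/30) = 2.857; Φ(0.897) = 81.5%.

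The claim reproduces. These are death rates, however. The protocol gives no rate for the composite and no prognostic strength for the baselines, so what follows rests on assumptions.

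**Chance imbalance.** With 30 per arm, the difference in means of a baseline variable has standard error √(2/30) = 0.258 SD under simple randomisation. P(|difference| > 0.3 SD) = 2(1 − Φ(0.3/0.258)) ≈ 25%.

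**Large-sample guide.** The adjusted variance is about (1 − R²) times the crude one, where R² is the share of outcome variance explained by the baselines. R² of 0.10, 0.20 or 0.30 multiplies the interval width by 0.95, 0.89 or 0.84. At n = 60 the gain is smaller, because the coefficients must be estimated.

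**Simulation at n = 60.** Assumed failure rates 40% (placebo) and 20% (active), two normal baseline covariates, and a logistic model standardised to a marginal risk difference, compared with the crude difference. Crude SE = √((0.24+0.16)/30) = 0.1155. Adjusted SE = 0.1155 × √(variance ratio); half-width = 1.96 × SE; power = Φ(0.20/SE − 1.96); equivalent N = 60/ratio.

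| Baselines | Variance ratio | 95% half-width | Power | Equivalent N |
|---|---|---|---|---|
| Crude analysis | 1.00 | 0.226 | 41% | 60 |
| No prognostic value | 1.02 | 0.229 | 40% | 59 |
| Weak (AUC about 0.68) | 0.97 | 0.223 | 42% | 62 |
| Moderate (AUC about 0.74) | 0.88 | 0.212 | 45% | 68 |
| Strong (AUC about 0.81) | 0.79 | 0.201 | 50% | 76 |

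Separate runs differ by up to about three percentage points in the ratio. Neither estimator shows material bias.

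**Closer to this endpoint.** A simulation with failure as a threshold on two measures, and entry truncated as in criterion 5, gave smaller gains: about 5% lower variance at a baseline-to-Day-4 correlation of 0.5-0.6, 8% at 0.7 and 15% at 0.8.

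**Number of covariates.** With three covariates of no prognostic value the ratio was 1.06, against 1.01-1.02 with one. This favours a short list.

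**The case against.** The crude comparison is unbiased under randomisation, and its exact interval and Fisher test need no model. An adjusted analysis is already planned, the WHO scale is only an example, and the covariate list is properly the SAP's business. In an estimation study with no success rule tied to the primary p-value, both results will be reported, and which comes first may look like taste. The gain rests on assumed rates and assumed prognostic strength, and was measured against the crude analysis, not against the planned adjusted model. With a model-based delta-method standard error, the standardised difference covered 93-94% and rejected 6-7% under the null, against 94-95% and 5-6% for the crude Wald interval, so part of an apparent gain can be a standard error that is too small.

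Much of this stands, and it rules out several stronger readings:

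- A reader might infer that the primary analysis is invalid or biased. It is neither.
- A reader might infer that no adjustment is planned, or only for the WHO scale. The text does not say so.
- A reader might infer that randomisation is unstratified. Section 11.2 names no factor, but says that the details are described separately.
- A reader might count SpO2 as an equally neglected baseline. Its failure criterion is a decrease, so its starting value already enters the endpoint in part.

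What does not fall is the status of the analyses. The protocol itself, not the SAP, makes the crude difference primary. The coverage point constrains the choice of standard error; with a suitable one, coverage and null rejection were close to those of the crude Wald analysis.

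**Conclusion.** The point holds as a worthwhile improvement, not as an error that undermines the trial. The main estimate leaves out two baseline measures that are already collected and closely tied to the failure definition. The effect on variance ranges from a loss of about 2-3% if they carry no information to a gain of about 3%, 12% or 20% if they are weakly, moderately or strongly prognostic. Power is 41% crude and between about 40% and 50% adjusted.

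These figures rest on assumed failure rates of 40% and 20%, 30 patients per arm and an assumed prognostic strength. It would be tempting to quote only the upper end, as if some 15 patients' worth of information were being thrown away. The documents support the direction of the argument but not that size, and the simulation nearer to the actual endpoint suggests the middle of the range or below.

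**What to change.** Before unblinding, state in the protocol and SAP that the main estimate for the Day 4 composite is the standardised (marginal) risk difference from a logistic model with treatment, baseline PaO2/FiO2 and baseline RR, the last two as continuous terms. Give its 95% interval from a small-sample-corrected influence-function standard error or a bootstrap, and specify a penalised fit if events are sparse. Report the crude difference with its exact interval and Fisher's test alongside.

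An adjusted odds ratio alone would not do the job: it targets a conditional effect, and its standard error does not shrink in the same way.

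The change needs wording only and no new data. It brings a slight reliance on a model, and a loss of about 2-3% of variance if the baselines turn out not to be prognostic.
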